#### Eligibility criteria for family physician offices (clusters) and family physicians

We will enroll family physician offices that see a minimum of 100 patients per week (see sample size calculation for justification). If it arises that multiple physician offices share the same waiting room, these will be considered as a single site given that all patients within the waiting room will be exposed to the intervention. We will include family physicians from the enrolled site who are willing to provide their Canadian Physician Surgeons Ontario number (a personal identifier) to allow linkage between the billing date for fee for service payments for patient visits and the date of donor registration. We will exclude family physicians if they primarily work at multiple sites because our administrative databases only allow linkage of patients to physicians but not to the location of patient visits.

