#### Eligibility criteria for patients

For our outcome analysis using routinely collected registry data, we will include any patients aged 16 years and older with a valid health card (all of whom are considered eligible to register for deceased organ in Ontario). These patients will have at least one outpatient visit during the period of interest with a family physician participating in this trial.

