##### Component 3 – Providing immediate opportunity to register

A secure Internet-enabled tablet (i.e., an iPad) will be added in each waiting room to give patients the immediate opportunity to register for organ donation online via a secure provincial website. Adding the tablet also aims to address beliefs about capability to register and acts as a prompt/cue to register, focusing their attention and prioritizing registration while they wait. Table 3 provides a further overview of intervention as per TiDIER criteria, and online additional materials provides detailed mapping of BCTs to theoretical domains informed by interview results). All materials will be in English only for this intervention. The location of the materials will be tailored according to the family physician office’s preferences.

**Table 3 Tab3:** Overview of the RegisterNow-1 intervention, as per Template for Intervention Description and Replication (TiDIER) criteria

TiDIER criteria	Description of intervention and quality control procedures
Brief name	RegisterNow-1 intervention
Why?	Patients are often unsure if they registered for organ donation. Many patients support organ donation but have not prioritized it and may not get around to it. Providing immediate opportunity to register for organ donation would address this barrier and leverage those already motivated to register
What materials?	Pamphlets designed to address previously identified barriers and enablers to organ donation registration, Internet-enabled tablet, and training material for office staff
What procedures?	Reception staff will check health cards for donor status, use a standard script to provide a pamphlet to patients and suggest to those that have not yet registered for organ donation that they can do so using the tablet in the waiting room. The pamphlet will describe ways the patient can register for organ donation (e.g., use the Internet-enabled tablet in the waiting room). Behavior Change Techniques (BCTs) are described in Table 2
Who provided?	Reception staff
How?	Face to face, paper and electronic
Where?	Family physician office waiting room
When and how much?	The intervention will be available between 2 and 14 weeks in duration (depending on the randomly allocated start date). For a given patient, they are likely only to be exposed to the intervention once unless they have a repeat visit during the period in which their practice is delivering the intervention

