### Outcomes

The primary outcome is the proportion of all patients aged 16 years and older who visited the office during each 2-week interval who are registered for deceased organ donation at 7 days following the family physician visit. We chose 7 days to ensure that patients have the opportunity, should they wish, to discuss their decision to register with their family or friends. However, we expect and have designed the intervention so that most of the registrations take place immediately (same day) during their family physician clinic visit; this is consistent with the observed barriers to registration. We designated prevalence of donor registration (rather than incidence of new registrations) as the primary outcome for the trial as it was important to measure the net effect of our cluster-level intervention on the overall prevalence of donor registration among all patients with visits to their family physician. Secondary outcomes are the proportions of unregistered patients aged 16 years and older who newly register for deceased organ donation within 7 days of visiting the family physician clinic, as well as at 1 day, 14 days and 30 days post visit.

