### Data collection methods/data management

We will ascertain baseline and outcome information from healthcare administrative databases housed at the Institute for Clinical Evaluative Sciences (ICES). Under section 45 of Ontario’s Personal Health Information Privacy Act, ICES is considered a prescribed entity. Health information custodians, such as physicians, can disclose personal health information to ICES without patient consent for the purpose of research. These databases can be linked via encoded identifiers. Specifically, we will use our list of recruited family physicians to link to the Ontario Health Insurance Plan (OHIP) billing datasets to identify the patients who visited our recruited family physicians and the dates at which they visited. We will then use the Registered Persons Database to obtain patient demographic information and their donor registration information (including date of registration).

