## Discussion

As far as we know, this study will be the first Canadian multi-site cluster randomized controlled trial of an intervention to increase donor registration delivered within family physician offices. As of 2017, organ donor registration rates in Ontario stand at 31%. Increasing donor registration rates in Canada remains an important component of the overall strategy to increase organ donation.

Our trial has several important strengths. First, our study integrates routinely collected administrative healthcare data in a clinical trial design. This population-level approach allows us to enroll and objectively collect behavioral data on *all* patients who visit a family physician clinic. Second, we use a behavior-change, theory-based approach to develop, inform and report our intervention, aiming to provide a novel behavior change-focused strategy to improving registration while simultaneously increasing the transparency and replicability of our intervention. Our intervention targets identified barriers and enablers using behavior-change theory based upon our qualitative work. Our intervention was also designed with substantial input from patients, family physicians, health psychologists and the provincial organ procurement marketing and communications team. Third, as opposed to involving research staff in the delivery, our intervention is entirely delivered by reception staff within family practice settings to ensure consistency with real-world settings.

A potential limitation for this trial is that we are unable to quantify the degree to which our intervention was delivered as intended. We will instruct each reception staff member to provide pamphlets to all patients who have not registered for organ donation upon checking their health card for eligibility. Although we can count the number of pamphlets that were given out, we will not ultimately know how many pamphlets were given to eligible patients (i.e., patients whose health cards did not have the *donor* status). Under the intention-to-treat principle, all patients with visits during the intervention periods will be analyzed as if they were exposed to the intervention.

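### Billing data do not show where a visit took place, and excluding only physicians who primarily work at multiple sites can leave off-site visits in the analysis under the trial office's condition

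*Protocol article*

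**What the plan says.** The protocol's section on eligibility of offices and physicians gives the exclusion and its reason together: "We will exclude family physicians if they primarily work at multiple sites because our administrative databases only allow linkage of patients to physicians". The same sentence goes on to say that the place of a visit cannot be linked. No threshold is attached to the word *primarily*.

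The section on patient eligibility admits anyone with "at least one outpatient visit during the period of interest with a family physician participating in this trial". The data collection section says the billing records of recruited physicians will be used "to identify the patients who visited our recruited family physicians and the dates at which they visited". Neither sets a condition on where the visit happened.

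The Outcomes section defines the primary outcome as "the proportion of all patients aged 16 years and older who visited the office during each 2-week interval" and are registered 7 days later. Table 3 gives the place of delivery as "Family physician office waiting room".

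The Discussion adds that, by intention to treat, "all patients with visits during the intervention periods will be analyzed as if they were exposed to the intervention".

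**The concern.** The protocol recognises that it cannot see visit location, and it answers with a restriction on physicians. That restriction can leave in a physician who is based mainly at the trial office but holds some outpatient sessions elsewhere. By the protocol's own account, that physician's off-site visits cannot be told apart in the data, and no later step removes them.

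In an intervention period, such a visit counts as exposed although the patient met no trial receptionist, pamphlet or tablet. In a control period it counts as a control visit of the office. No exposure is mistaken there, but the patient is still outside the outcome's stated population.

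Intention to treat does not settle the matter. That principle keeps people in the analysis under the condition of the cluster they attended, and an off-site patient did not attend the cluster at that visit. The limitation in the Discussion is a different one: it concerns whether receptionists gave pamphlets to the right people among those who did attend. What is at stake is a diluted effect estimate and lost power in a trial with only six clusters.

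**Working it through.** **Inputs from the protocol** (Table 1 and Sample size): 6 offices, one per sequence; 7 periods of 2 weeks; m = 250 encounters per office-period; control proportion 0.50, intervention proportion 0.60; ICC ρ = 0.06; cluster autocorrelation 0.8; two-sided 5%; 80% power; 10,500 patients.

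**Input not in the protocol**: f, the share of linked visits that took place off-site. I assume 5%, 10% and 20%, equal across offices and periods, with no intervention effect on those visits.

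**Step 1. Reproduce the plan's own figure.**
- Total: 6 × 7 × 250 = 10,500, as stated.
- Unclustered total: n = 2 × (1.96 + 0.8416)² × (0.25 + 0.24) / 0.10² = 769.
- Within-period inflation: 1 + 249 × 0.06 = 15.94.
- Correlation of an office's means between periods: r = 250 × 0.06 × 0.8 / 15.94 = 0.753.
- Stepped-wedge factor with L = 6 steps: 3L(1 − r)(1 + Lr) / [(L² − 1)(2 + Lr)] = 0.1076.
- Design effect: 15.94 × 0.1076 = 1.715.
- Patients per period: 769 × 1.715 = 1,319. Clusters: 1,319 / 250 = 5.28, rounded up to 6. The stated six clusters reproduce.

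**Step 2. Power actually available at six clusters.** I computed the generalised least squares variance of the 6 × 7 design with fixed period effects. With σ² = (0.25 + 0.24)/2 = 0.245, an office-period mean has variance σ²[0.06 + 0.94/250], and two periods of one office have covariance σ² × 0.06 × 0.8. The standard error of the effect is 0.0335. Power at 0.10 is Φ(0.10/0.0335 − 1.96) = 84.8%, and the difference detectable with 80% power is 2.80 × 0.0335 = 0.094. The margin above 80% comes from rounding 5.28 up to 6.

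**Step 3. Leave off-site visits in.** Analysed effect = (1 − f) × 0.10 + f × 0. Power = Φ(effect/0.0335 − 1.96).

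**Step 4. Remove them.** The effect stays 0.10, m becomes 250(1 − f), and the standard error is recomputed as in Step 2.

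| Assumed f | Effect, visits left in | Power, left in | m, visits removed | Power, removed |
|---|---|---|---|---|
| 0% | 0.100 | 84.8% | 250 | 84.8% |
| 5% | 0.095 | 81.0% | 237.5 | 84.4% |
| 10% | 0.090 | 76.7% | 225 | 83.9% |
| 20% | 0.080 | 66.6% | 200 | 82.8% |

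Step 3 holds the standard error at its Step 2 value. Recomputing it for the smaller intervention proportion gives 80.9%, 76.5% and 66.3%, which does not change the picture. Power reaches 80% at f = 1 − 0.0938/0.10, about 6%.

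The two right-hand columns show why removal is cheap: with ρ = 0.06 and hundreds of patients per office-period, losing some of them hardly moves the standard error.

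**The case against.** The strongest reply is that the plan saw this problem and acted on it. It states the data limit, removes the physicians likely to have the most off-site work, and counts outpatient visits only, which may exclude some other settings. Physician billing can fairly be called a measurable proxy for office attendance. A cut-off for *primarily* is a detail that a condensed article may leave to the full protocol. All of that stands, and it means the remaining off-site share may be small. It does not close the gap. If billing does not carry location, an analysis plan cannot separate these visits without information from the physicians, and the protocol describes collecting none.

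A reader might infer several stronger things that the documents do not support:

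- **That the rule fails its purpose, or that physicians with regular days elsewhere are known to be enrolled.** The rule partly works, the word *primarily* is open to a strict reading, and nothing shows who was retained.
- **That the eligibility and outcome sections flatly contradict each other.** They differ only for off-site visits of retained physicians.
- **That power falls from exactly 80%, to 71%, 61% and 50% at f = 10%, 20% and 30%.** That start ignores the rounding up to six clusters. A large f is also hard to reach, because f is averaged over an office's physicians and those with most off-site work are the likeliest to be excluded.
- **That a different patient mix biases the effect.** No section describes off-site patients. If their share is stable, the office random intercept takes up the difference in level, and the model adjusts for age, sex and income. Bias would need the share to shift at crossover.
- **That a false positive is at risk.** Dilution works toward no effect.

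**Conclusion.** The point holds as a gap in ascertainment that is cheap to close. The set that would be analysed can be wider than the population named in the primary outcome, and no described step narrows it.

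The size is unknown, because f is unknown. An f of about 6% uses up the margin above 80% power, and an f of 20% would bring power to about 67%. These figures assume that off-site visits carry no intervention effect and that f is constant. The first assumption may be slightly pessimistic, since staff materials encourage physicians to raise donation and they might do so elsewhere. The power figures are normal approximations, and the planned Kenward-Roger correction would lower all of them. If every retained physician sees outpatients only at the trial office, f is zero and nothing is lost.

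**What to change.** Before data extraction, under the written linkage consent that the Ethics section already provides for, ask each participating physician on which days they work at another site during the 14 weeks. Exclude billing dates on those days, by the same rule in control and intervention periods, and state this in the patient eligibility section so that it matches the primary outcome as closely as the data allow. Add a sensitivity analysis limited to physicians whose outpatient work is all at the trial office.

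Two simpler edits are less suitable. Requiring in the text that the visit be at the office cannot be applied directly, because location is not in the data. Striking *primarily* would drop every physician with any second site, an unknown number, and would narrow a pragmatic trial.

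The cost is one extra question per physician and a date filter at extraction. Some legitimate visits will be lost on days split between sites, and the filter will be imperfect where off-site days are irregular. At the assumed shares up to 20%, the power given up by dropping visits is at most about 2 points (84.8% to 82.8%).

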#### Eligibility criteria for patients

For our outcome analysis using routinely collected registry data, we will include any patients aged 16 years and older with a valid health card (all of whom are considered eligible to register for deceased organ in Ontario). These patients will have at least one outpatient visit during the period of interest with a family physician participating in this trial.

#### Intervention development and description

To inform the development of this intervention, we identified theory-based barriers and enablers to organ donation registration. We conducted semi-structured interviews with 20 patients from one family practice (nine of which had not registered for organ donation). The interview guide was based on the Theoretical Domains Framework [15]. Findings showed that patients were largely aware and motivated to register for organ donation. However, many patients were unclear on how to register and whether they were eligible and did not realize that their donor status is on the back of their health card. In Ontario, Canada, the donor registration status is found on the health card rather than the driver’s licence. It reflects registration status at the time that the card was issued, where cards need to be renewed every 5 years. Many patients also assumed their health status made them a poor candidate. That said, many were clear on the benefits of registration to themselves and others. Importantly, a key barrier involved a lack of priority and not getting around to it. We therefore leveraged these findings to design an intervention to provide an opportunity to register, to address barriers and enablers and to prompt them to consider registration in the waiting room of a family physician office as a novel and suitable setting for considering this health decision (see Additional file 2: Table S2).

We then identified possible methods of delivery that can be feasibly implemented within a family physician waiting room. Considering the time constraints and competing demands faced by many family physicians in their office, we identified practice reception staff as a resource for providing components of the intervention. Receptionists are the first point of contact that patients have with the practice, which inherently involves requesting the health card at the time a patient presents to the counter upon arrival. As donor status is listed on the health card, it can be easily verified. Reception staff are ideally positioned for providing physical materials (pamphlets) and prompting the use of tablets or cellphones in the waiting room. We linked possible BCTs to identified barriers and enablers from the interviews. We used an iterative process to develop and operationalize BCTs and methods of delivery with stakeholders (citizen panel, researchers, family physicians and provincial organ procurement organization). Intervention materials including the training protocols will be uploaded to our website and included with the trial results publication.

#### Detailed description of the intervention

The intervention involves three key components: (1) case finding by reception staff to identify patients who have not yet registered for organ donation by checking the back of their health card, (2) reception staff providing pamphlets designed to deliver BCTs designed to address previously identified barriers and enablers and (3) providing an Internet-enabled tablet in the waiting rooms to enable immediate and secure online registration while waiting for their appointment [16, 17]. The theoretical basis of the intervention is consistent with Social Cognitive Theory and triadic reciprocal determinism between the person (and their cognitions), their behavior and their environment [18, 19], and a basis in a dual process model of behavior change emphasizing a role for reflective as well as impulsive, automatic influences on behavior through changes in the physical and social environment and prompts/cues to behavior [20, 21]. Table 2 describes the BCTs to be delivered within each intervention component, linked to the specific barriers and enablers targeted by each technique as described by the Theoretical Domains Framework, and outlined in more detail below [14, 15, 22].

**Table 2 Tab2:** RegisterNow-1 intervention description

Component 1: case finding		Component 2: pamphlet		Component 3: immediate opportunity to register	
Who delivered?: Reception staff		How delivered?: Paper pamphlet provided by: reception staff		How delivered?: Tablet	
BCT	Domain	BCT	Domain	BCT	Domain
Instruction on how to perform the behavior	Knowledge (procedural)	Instruction on how to perform the behavior	Knowledge (procedural); skills; beliefs about capabilities	Adding objects to the environment	Beliefs about capabilities; environmental context and resources; memory, attention and decision processes; behavioral regulation
Social support (practical)	Knowledge (procedural)	Information about others’ approval	Social influences; goals; emotion; beliefs about consequences	Prompts/cues	Memory, attention and decision processes
Prompts/cues	Memory, attention and decision processes	Credible source	Social influence; emotion; beliefs about consequences		
Information about others’ approval	Social influences	Social comparison	Social influences		
		Prompts/cues	Memory, attention and decision processes		
		Verbal persuasion of capability	Beliefs about capabilities; Knowledge		
		Vicarious consequences	Beliefs about capabilities; beliefs about consequences; emotion		
		Information about social and environmental consequences	Beliefs about consequences; social influences; social/professional role and identity		
		Salience of consequences	Beliefs about consequences; social influences		
		Information about emotional consequences	Beliefs about consequences; emotion		

*BCT* behaviour-change technique, *Domain* specific barrier/enabler targeted by the BCT, based on domains described by the Theoretical Domains Framework

##### Component 1 – Reception staff case finding

First, reception staff will verify the organ donor registration status of patients upon their arrival at the clinic on the provincial health card that patients must provide to receive healthcare services from their family physician. As reception staff already request a patient’s health card during their visit, this step is designed to fit within existing work routines rather than increasing any workload. Reception staff will provide instruction on how to perform the behavior, social support (practical) and prompts/cues to address citizens’ procedural knowledge about how to check whether they are registered and how to register, and to prompt them to do so if they wish. They will provide a pamphlet and indicate that they can register while they wait by using the tablet in the waiting room or their cellphone.

